### 5.9.2. Study discontinuation

If any of the following criteria are met, the PI or SI will discontinue the study in the subject.

- 1) When progression of the primary disease requiring concomitant use of prohibited drugs or concomitant therapy is recognized, as judged by the PI or SI.
- 2) When the subject requests discontinuation of the study.
- 3) When a subject is found to be ineligible after his/her registration.
- 4) Other cases in which the PI or SI determines that the subject is unable to receive DC/Gal.

When a subject who meets the criteria for discontinuation is identified after the start of DC/Gal or iPS-NKT cell administration, the PI or SI should explain this to the subject, discontinue the study, and take appropriate measures.

In the case of discontinuation due to adverse events (including abnormal changes in laboratory test values), necessary examination and observation should be conducted until it is determined that the subject can be discharged or transferred to another hospital. For adverse events for which a causal relationship with DC/Gal or iPS-NKT cell cannot be denied, observation should be continued as much as possible until symptoms recover or become mild, in principle.

The PI or SI should record the date of discontinuation, reason for discontinuation, and other necessary information. In addition, the PI or SI should perform the stipulated items at the time of discontinuation as possible.

In the case of discontinuation, the "date of discontinuation" shall be the date when the PI or SI decides to discontinue the study, not the date when the event that is the reason for discontinuation occurs or becomes known.

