## 5.2. Dose Limiting Toxicity (DLT)

DLT is defined as the following adverse events observed during the DLT assessment period, in which a causal relationship with auto-DC/Gal or iPS-NKT cell cannot be denied. Grading is determined according to the CTCAE ver.5.0 translated in Japanese by the Japan Clinical Oncology Group (JCOG).

- 1) Grade 4 or higher hematological toxicities
- 2) any non-disease-related blood toxicity requiring any transfusion or granulocyte-colony stimulating factor (G-CSF) administration
- 3) grade 3 or higher non-hematological toxicities (excluding transient clinical laboratory abnormalities, diarrhea, nausea, vomiting, or other manageable systemic symptoms that recovered to grade 2 or below under appropriate treatments)
- 4) AEs lead to blood transfusion.

If the PI suspects the occurrence of DLTs, the PI can consult the Independent Data Monitoring Committee (IDMC), and the IDMC determines the continuation or termination for the patient. Subjects who do not complete the DLT assessment period for reasons other than DLT will not be considered DLT evaluable cases and then another

subject will be supplemented in the same dose cohort.

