## 5.9. Criteria of treatment and study discontinuation for each subject

### 5.9.1. treatment discontinuation

If any of the following criteria are met, the PI or SI will discontinue administration of DC/Gal or iPS-NKT cell. If administration is discontinued, the subject will be shifted to the observation period from the date when the decision to discontinue administration was made, and testing and assessment will be continued in accordance with the study schedule.

- 1) DLT occurs after administration of DC/Gal, or all adverse events of Grade 3 or higher that occurred during the study period do not recover or improve to Grade 1 or clinically manageable Grade 2 by the time immediately before administration of DC/Gal or iPS-NKT cell.
- 2) Subject develops an infectious disease requiring treatment that does not recover or improve to Grade 1, or does not improve to a clinically manageable Grade 2 by the time immediately prior to administration of DC/Gal or iPS-NKT cell.
- 3) SpO2 (room air) is maintained below 90%.
- 4) Grade 2 or higher on the mMRC shortness of breath scale (see Appendix 3) in the examination before administration of DC/Gal or iPS-NKT cells.
- 5) Requirement for the discontinuation from the subject.
- 6) Other cases in which the need to discontinue the administration of DC/Gal or iPS-NKT cell to the subject are recognized by the PI or SI.

The PI or SI should record the date of discontinuation, reason for discontinuation, and other necessary information.

In the case of discontinuation of DC/Gal or iPS-NKT cell administration, the "date of discontinuation" is not the date when the event causing the discontinuation occurred or became known, but the date when the PI or SI decided to discontinue.

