#### 7.1.3.4. Study Discontinuation

Within 7 days of the decision by the PI or SI to discontinue the study, the following will be performed as possible. However, if post-treatment is to be initiated, the following must be performed prior to the start of post-treatment.

- Body Weight
- ECOG PS
- Hematology
- Blood Biochemistry Test
- Urinalysis
- Pregnancy test (for women with childbearing potential only)
- Chest X-ray
- Adverse event evaluation
- Contrast-enhanced CT (or contrast-enhanced MRI) scan (tumor evaluation)
- Anti-HLA antibody test

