### 8.4. Reportable Adverse Events and Quality Defects

- 1) All adverse events occurring from the date of consent to the last day of the observation period (at the time of discontinuation) should be reported regardless of whether or not they are causally related to DC/Gal or iPS-NKT cells, and the patients should be observed until they recover from the adverse events or the last day of the observation period (at the time of discontinuation). All adverse events judged to be causally related to DC/Gal or iPS-NKT cells should be reported until the end of the study period.
- 2) All information on quality defects occurring during the study period shall be reported.

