### 10.1.3. Subject population conforming to the research protocol (per protocol set : PPS)

Subjects without the following serious violations of the provisions of the research protocol, including study methods and concomitant therapies.

Violation of selection criteria, exclusion criteria, concomitant use of prohibited drugs, or concomitant use of prohibited therapies

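### A subject found ineligible after receiving cells must leave the study: scheduled visits and all-cause adverse-event reporting stop, and inside the DLT window the subject is replaced

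*Protocol*

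**What the plan says.** Protocol section 5.9 has two kinds of stop. Under 5.9.1, when administration is stopped, "the subject will be shifted to the observation period from the date when the decision to discontinue administration was made", and testing continues to schedule. Ineligibility is not named among the 5.9.1 criteria. Section 5.9.2 ends the study itself and is mandatory: "If any of the following criteria are met, the PI or SI will discontinue the study in the subject". Its criterion 3 reads "When a subject is found to be ineligible after his/her registration". The text below the list covers the case "When a subject who meets the criteria for discontinuation is identified after the start of DC/Gal or iPS-NKT cell administration" and makes no exception for dosed subjects.

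Three other sections set the consequences:

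- Section 7.1.3.4: "Within 7 days of the decision by the PI or SI to discontinue the study, the following will be performed as possible".
- Section 8.4: "All adverse events occurring from the date of consent to the last day of the observation period (at the time of discontinuation) should be reported". A further sentence keeps causally related events reportable to the end of the study period.
- Section 5.2: "Subjects who do not complete the DLT assessment period for reasons other than DLT will not be considered DLT evaluable cases". Another subject is then added to the same dose cohort, and section 10.1.1 repeats the replacement.

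Section 5.11 requires necessary examination and observation of any discontinued subject until discharge or transfer is medically possible. Under section 10.1.1 a registered subject given auto-DC/Gal belongs to the safety population.

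**The concern.** Each product is given once (section 5.6), with iPS-NKT cells nominally on Day 6 of the study calendar. After that day there is no study treatment left to withhold, so removing a subject from the study takes away only observation. An eligibility error discovered later does not make that subject's experience of the cells uninformative. In a first-in-human combination with at most 12 analysed subjects, each dosed subject's safety record is a material share of the evidence. Replacement also means exposing one more patient to obtain information that the first could still have supplied.

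**Working it through.** **1. The plan's own figure.** Section 10.2 gives a sample size of 2 to 12. The minimum is two consecutive DLTs at the first dose. The maximum is 6 subjects × 2 doses = 12. Both reproduce. Replaced subjects come on top of the 12.

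**2. The calendar.** Nominal days, ignoring visit allowances: auto-DC/Gal on Day 1 and iPS-NKT on Day 6. The DLT window closes 14 days after iPS-NKT (section 5.1), so on Day 6 + 14 = Day 20. Section 5.1 also places the first day of the observation period 14 days after iPS-NKT, so observation Day 28 = Day 20 + 27 = Day 47. Section 7.1.3.5 dates that first day differently, at 28 days after iPS-NKT; the section 5.1 definition is used here.

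**3. What a withdrawal removes.**

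| Withdrawn on | DLT-window days unobserved (20 − day) | Scheduled follow-up lost (47 − day) |
|---|---|---|
| Day 7 | 13 | 40 |
| Day 10 | 10 | 37 |
| Day 13 | 7 | 34 |
| Day 19 | 1 | 28 |

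The last column is an upper limit. If the termination visit takes place 7 days after the decision, the Day 10 figure is 37 − 7 = 30. A subject found ineligible after about Day 20, or after a DLT has occurred, does not become non-evaluable under section 5.2 and loses only the later scheduled visits.

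**4. Effect on the 3+3 decision.** With DLT risk p, a dose passes on 0/3, or on 1/3 followed by 0/3:

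P(pass) = (1 − p)³ + 3p(1 − p)² × (1 − p)³

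At p = 0.20 this is 0.512 + 0.384 × 0.512 = 0.709.

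The protocol gives no rate of late-found ineligibility, so take three assumptions: a fraction q of dosed subjects is found ineligible inside the window, their DLT risk is r, and under the written rule none of their DLTs is counted. Replacing them leaves the pass probability at 0.709. Keeping them gives a mixed risk of (1 − q) × 0.20 + q × r:

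| q | Kept, r = 0.20 | Mixed risk, r = 0.40 | Kept, r = 0.40 | Dosed per 12 evaluable, 12/(1 − q) |
|---|---|---|---|---|
| 5% | 0.709 | 0.21 | 0.687 | 12.6 |
| 10% | 0.709 | 0.22 | 0.665 | 13.3 |
| 20% | 0.709 | 0.24 | 0.622 | 15.0 |

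The difference runs from nil at equal risk to 0.709 − 0.622 = 0.087, about 9 percentage points, at q = 20% with doubled risk. The calculation is simplified: a DLT that occurs before the ineligibility is found would still count.

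**The case against.** The strongest answer is that the subject does not vanish. Section 8.4 keeps related events reportable, and a DLT is by definition an event whose relation cannot be denied. Section 5.11 requires observation until discharge or transfer, and subjects in the DLT window are in principle in hospital. Sections 8.7 and 8.8 require suspected product-related disease to be reported. The IDMC weighs all safety information before a dose change (section 10.6). Eligibility is discussed with at least two coordinating-committee physicians before registration (section 5.4.2), so late discoveries should be rare.

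All of this stands, and it rules out several stronger readings:

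- A reader might infer that adverse-event collection ends altogether. It does not: only all-cause reporting and the scheduled visits end. The synopsis entry on duration of participation ties an early end to the subject's request or to difficulty in observing, and does not name ineligibility found by the investigator.
- A reader might infer that every dosed subject found ineligible is lost to the DLT analysis. That holds only inside the window and without a DLT.
- The per-protocol exclusion in section 10.1.3, "Violation of selection criteria, exclusion criteria, concomitant use of prohibited drugs, or concomitant use of prohibited therapies", might suggest a conflict with early withdrawal. There is none: the termination assessment includes contrast CT or MRI, so such subjects can still supply efficacy data to the full analysis set.
- Criterion 1 of section 5.9.2 (progression needing prohibited therapy) might look like the same fault. Ending follow-up when another anticancer therapy starts is a debatable trade-off over attribution, and section 7.1.3.4 requires the assessments before that therapy begins.

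What the objection does not answer is detection and counting. A reporting duty schedules no visit or laboratory test. Observation under section 5.11 stops at discharge or transfer. Section 5.2, read literally, still leaves a subject non-evaluable if a qualifying event is reported after withdrawal, because the window was left for a reason other than DLT.

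**Conclusion.** The point holds in limited form. For a dosed subject found ineligible, section 5.9.2 ends scheduled visits and all-cause adverse-event reporting although no treatment may remain to be stopped. Inside the DLT window, without a DLT, it also makes the subject non-evaluable and calls for a replacement. The size depends on timing: withdrawal on Day 10 forgoes 10 of the 14 post-iPS-NKT DLT days and up to 37 scheduled days.

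One might conclude that the rule biases the trial towards calling a dose tolerable. The documents do not support that. At equal DLT risk the calculation shows no change, and the shift of about 9 points needs both a 20% rate and doubled risk, neither of which comes from the protocol. The gain from changing the rule is safety information kept and replacement avoided. It is worth an amendment, but it does not threaten the trial's conclusions.

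**What to change.** Reconcile sections 5.9.1, 5.9.2, 5.2 and 8.4 for subjects who have received either product:

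- Late-found ineligibility alone does not end scheduled safety visits, laboratory tests or adverse-event collection. These continue to observation Day 28 unless consent is withdrawn.
- The subject stays DLT-evaluable if the DLT window is completed or a DLT occurs.
- The per-protocol exclusion in section 10.1.3 stays as it is.

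This concerns observation and counting only. No change to any treatment rule is proposed, including whether a subject found ineligible between the two products receives the second. A subject who never receives iPS-NKT cells cannot complete the window as section 5.1 defines it, and would still be replaced unless a DLT occurs.

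The cost is protocol wording and a few visits already defined in the study calendar for the rare subject affected.

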## 5.10. Concomitant drugs and therapy

### 5.10.1. Permitted concomitant drug/therapy

- Palliative and supportive care for the primary disease
- Palliative radiation therapy for local pain management may be administered during the study if:
  - The irradiated area covers less than 10% of the total bone marrow
  - The irradiation field does not include the evaluation lesion
- Any transfusion therapy as a response to adverse events thought to be caused by DC/Gal or iPS-NKT cell. Such adverse events shall be considered DLT.

### 5.10.2. Record on concomitant drug/therapy

For concomitant drugs and therapies listed in 5.10.3. that were used from the administration of DC/Gal or iPS-NKT cell until the end of the last observation (at the time of discontinuation), record the drug name (trade name or generic name), duration of administration, and purpose of administration. For concomitant therapy, record the name of the therapy, duration of therapy, and purpose of therapy.

### 5.10.3. Prohibited drug/therapy

In this study, DC/Gal or iPS-NKT cell will not be administered in combination with the following drugs or therapies. If it is necessary to use them clinically, it should be treated as a deviation to avoid immediate risk and reported to the record and the head of the medical institution.

- Corticosteroids (methylprednisolone 10 mg/day or more or equivalent) or immunosuppressive drugs taken or injected, other antineoplastic agents, radiation therapy, or surgery including tumor resection

- Any transfusion therapy (except as noted in 5.10.1).

#### 5.11. Actions to be taken after discontinuation or termination of the study

Subjects who discontinue or terminate the study will be subjected to necessary examination and observation, and appropriate measures will be taken as necessary, until it can be medically determined that the subject can be discharged or transferred to another hospital.

## 6. Specified cell processed product

### 6.1.1. Packaging/label of iPS-NKT cell

Gas-exchangeable plastic test tubes containing iPS-NKT cell are stored in a plastic pack capable of supplying CO2 (AnaeroPack®CO2) and are further encased in a transport box (TACPack®37) that can be kept at 37°C for heat insulation during transport. In addition, the plastic pack containing the iPS-NKT cell is clearly stated with the following information.

- 1) For experimental use only
- 2) Name, title, and address of the person conducting the study
- 3) Cells, transgenes, or identification code
- 4) Serial number or serial symbol
- 5) Storage method and validity period (if necessary to be specified)

An example of iPS-NKT cell product label

|                                                                                                                         |                   |
|-------------------------------------------------------------------------------------------------------------------------|-------------------|
| 
iPS-NKT for Clinical Trial
 |                   |
| Serial number: NKT-                                                                                                     | (Date of melting) |
| Packaging form/number of tubes (50 mL tubes):                                                                           |                   |
| Component cells: Human iPS cell-derived NKT cells                                                                       |                   |
| Expiration date: 6 hours after shipment and within 3 hours after preparation                                            |                   |
| Date of shipment: yyyy/mm/dd, hh:mm                                                                                     |                   |
| Storage conditions: 37°C under 5% CO 2 (Allowance: 33 - 38°C)                                                |                   |
| PI: [name], Assistant Professor                                                                                |                   |
| Chiba University Hospital [name]                                      |                   |

### 6.1.2. Packaging/label of auto-DC/Gal

The auto-DC/Gal-filled micro-injectable syringe is placed in a bag and further packaged in a shipping box (TACPack®0208Re-2A-SC) that can be maintained at room temperature (4~25°C) for temperature control during transportation. In addition, the following is clearly stated on the bag containing the auto-DC/Gal.

- 1) Serial number: A2023xxx-000x-DC
- 2) Manufacturing Date and Time: yyyy/mm/dd, hh:mm
- 3) Expiration for administration: 2hrs after shipment
- 4) For experimental use only

## Example of label

|                                                             |                  |
|-------------------------------------------------------------|------------------|
| For use only on clinical trial                              | A2023xxx-000x-DC |
| Packaging form/number of tubes: Micro-injectable syringe/ 1 |                  |
| Date of shipment: YYYY/MM/DD, HH:MM                         |                  |
| Expiration for use: 2hours after shipment                   |                  |

## 6.2. Administration and dispensing methods

### 6.2.1. Administration and dispensing methods of iPS-NKT cell

- 1) After subject registration, the PI notifies RIKEN of the administration date, dose, etc.
- 2) RIKEN delivers the iPS-NKT cell to the PI of the study site prior to the administration of the iPS-NKT cell, based on the notification from the PI of the administration date, dosage, etc.
- 3) The administrator of the iPS-NKT cell line at the study site will manage the iPS-NKT cell in accordance with the "Procedure for Management of Specified Cell Processed Products" provided by the PI through the head of the study site
- 4) The timing and method of dispensing shall be in accordance with the separately prescribed procedure.

### 6.2.2. Management method of auto-DC/Gal

- 1) After the subject registration, the PI informs the Manufacturing Department of Chiba University Hospital Center for Advanced Medicine of the administration date, dose, etc.
- 2) The Manufacturing Department of the Chiba University Hospital Center for Advanced Medicine delivers auto-DC/Gal to the PI prior to administration, based on the information from the PI regarding the administration date, dosage, etc.
- 3) The administrator of the auto-DC/Gal at the study site manages the auto-DC/Gal in accordance with the "Procedures for the Management of Specified Cell Processed Products" provided by the PI through the head of the study site.

## 7. Method and Timing of Observations/tests/assessments

### 7.1. Study Schedule and Procedure

The schedule for conducting observations, tests, and assessments is shown in Table 19. The PI or SI should conduct the observations, tests, etc. according to the schedule. Procedures that can be performed by study coordinators, such as subject background investigation and blood tests, may be performed by the study coordinators under the supervision of the PI.

**Table 16 Study Calendar**

|                                           |   | Screening  | DC/Gal Prep. | Treatment Period |    |   |   |    |    | Observation Period  |                 |    | Termination |
|-------------------------------------------|---|------------|--------------|------------------|----|---|---|----|----|----------------------------------|-----------------|----|-------------|
| Day                                       |   | -42~
-8 | -7           | 1                | 6  | 7 | 8 | 13 | 19 | 1                                | 15              | 28 | —           |
| Allowance (days)                          |   |            |              | +3               | +3 | — | — |    | ±3 | ±3                               | ±7              | ±7 | +7          |
| Informed consent                          | ● |            |              |                  |    |   |   |    |    |                                  |                 |    |             |
| Demographics                              |   | ●          |              |                  |    |   |   |    |    |                                  |                 |    |             |
| Eligibility                               |   | ●          |              |                  |    |   |   |    |    |                                  |                 |    |             |
| Pregnancy test a)              |   | ●          |              |                  |    |   |   |    |    |                                  |                 | ●  | ●           |
| Infection test b)              |   | ●          |              |                  |    |   |   |    |    |                                  |                 |    |             |
| Chest X ray                               |   | ●          |              |                  |    |   |   | ●  |    | ●                                | ●               | ●  | ●           |
| ECG                                       |   | ●          |              |                  |    |   |   |    |    |                                  |                 |    |             |
| Enhanced CT or MRI                        |   | ●          |              |                  |    |   |   |    |    |                                  | ● h) |    | ●           |
| DC/Gal preparation                        |   |            | ●            |                  |    |   |   |    |    |                                  |                 |    |             |
| DC/Gal injection                          |   |            |              | ●                |    |   |   |    |    |                                  |                 |    |             |
| iPS-NKT cell administration c) |   |            |              |                  | ●  |   |   |    |    |                                  |                 |    |             |
| CBC/Laboratory test                       |   | ●          |              | ●                | ●  |   |   | ●  |    | ●                                | ●               | ●  | ●           |
| Coagulation test                          |   | ●          |              |                  | ●  |   |   |    |    |                                  |                 |    |             |
| Urology                                   |   | ●          |              | ●                | ●  |   |   |    |    | ●                                | ●               | ●  | ●           |
| Vital sign d)                  |   | ●          | ●            | ←————→           |    |   |   |    |    |                                  |                 |    |             |
| Body weight                               |   | ●          |              | ●                | ●  |   |   | ●  |    | ●                                | ●               | ●  | ●           |
| ECOG PS                                   |   | ●          |              | ●                | ●  |   |   |    |    | ●                                | ●               | ●  | ●           |
| mMRC                                      |   |            |              | ●                | ●  |   |   |    |    |                                  |                 |    |             |
| PK/PD e)                       |   |            |              |                  | ●  | ● |   | ●  |    |                                  |                 |    |             |
| Immune cell assessment f)      |   |            |              | ●                | ●  |   | ● | ●  |    | ●                                |                 |    |             |
| AEs                                       |   | ←————→     |              |                  |    |   |   |    |    |                                  |                 |    |             |
| DLTs under hospitalization g)  |   |            |              | ←————→           |    |   |   |    |    |                                  |                 |    |             |
| HLA test                                  |   | ●          |              |                  |    |   |   |    |    |                                  |                 |    |             |
| Anti-HLA antibody                         |   | ●          |              |                  | ●  |   |   |    |    | ●                                |                 |    | ●           |

(a) Perform only in women of childbearing potential. Perform a urine qualitative test.

(b) Infectious disease tests include HIV antibody, HTLV-1 antibody, HBs antigen, HBs antibody, HBc antibody, and HCV antibody. If the HBs antigen is negative and the HBs antibody test or HBc antibody test is positive, the HBV-DNA quantitative test is performed. If the HCV antibody test is positive, the HCV-RNA quantitative test is performed.

(c) Secure the route of administration of the investigational product 1 week prior to the first administration date (allowance based on 1 week prior to the first administration date: -14 to +7 days). As described in the Administration Method section, there are two methods of administering the investigational product (method of securing the route of administration): the port method (e.g., for maxillary cancer) or the Selsinger method. In the case of the port method, a port is implanted under local anesthesia in an IVR room, and the investigational product is administered through the implanted port after confirming that there are no signs of infection in the wound. In the case of the Selsinger method (tongue cancer, etc.), the tip of the catheter is guided into the tumor-feeding artery in the IVR room, and the investigational product is administered directly.

(d) Vital signs shall include body temperature, pulse rate, respiratory rate, SpO2, and blood pressure (systolic and diastolic), and additional tests (chest X-ray, hematological and serological tests, blood gas tests, etc.) may be added as necessary based on the judgment of the PI or SI.

(e) The blood collection schedule for PK/PD and blood cytokine measurements will be as shown in Table 20

(f) Isolate PBMCs from blood samples and stain for cell surface markers.

(g) During the DLT evaluation period (from the first dose to Cycle 2 Day 14) and for 7 days after the third dose of the investigational product, the subject will be carefully monitored for safety by hospitalization in principle. In addition, the results of laboratory tests and medical examinations after the seventh day of administration of the investigational product (Day 8 of each cycle) should show that no Grade 2 or higher non-hematological toxicity or Grade 3 or higher hematological toxicity has occurred, and that the site and home health care facility can be contacted in the event of an adverse event and that the patient can be contacted promptly in an emergency. The PI or SI may stay overnight or leave the hospital at his/her own discretion only when a system is in place to contact the site and home health care facility in the event of an adverse event and to contact the patient promptly in an emergency.

(h) Tumor biopsy will be performed before administration of auto-DC/Gal and/or within 2 days of iPS-NKT cell administration only in subjects who are judged by the PI or SI to be capable of biopsy from the tumor under infiltration or local anesthesia, and who have given consent for tumor biopsy.

(i) Cycle 1 Day 14 contrast CT scan (tumor evaluation) will be performed prior to Cycle 2 transition.

(j) If the administration of the investigational product is discontinued, the observation period will begin at the later of the end of the cycle of administration of the investigational product immediately prior to discontinuation (2 weeks after the last administration of the investigational product) or the date on which the decision to discontinue administration was made.

